**Perceived effect (acceptability)**
How has using the tool impacted your or the staff’s workload? Do you have examples?Was there something that you learned from the tool that you think is valuable to your work? To your relationship with clients?Have you noticed any changes in your or the staff’s relationship with clients as a result of using the tool?Have you noticed any changes in how clients have approached their housing search as a result of using the tool?
**Ease of implementation (implementation)**
What were some facilitators or challenges to recruiting participants?What were some facilitators or challenges to the use of the tool in your meetings? (eg, leadership support, internet stability, tech comfort, meeting duration, and client disinterest)
**Outcome appropriateness (implementation)**
Were the outcomes of knowledge, self-efficacy, and staff trust appropriate for the tool?Would you add other outcomes to consider? If so, what would they be, and why?
**Perceived usability**
Can you describe how (easy or difficult) it was to navigate the tool? See the information in the tool? Guide clients on how to use the tool?How relevant was the information presented by the tool to your discussions with clients?Did any of the content help start a conversation? Why or why not?How would you explain the tool to a client? To another staff member?
**Dissemination**
What suggestions do you have for disseminating the tool to staff and clients in the rest of the organization? Other agencies?How could the tool be used by others (eg, housing specialists, case managers, social workers, lawyers, real estate brokers, and other domestic violence advocates)? Probe: Who else could use the tool? Could it be used to build capacity (eg, training) or standardize information sharing?

### Feasibility Criteria

As recommended by Thabane et al [44], we established formal Stop or Go criteria to evaluate the success of the feasibility study. A Stop outcome states that the subsequent large-scale trial is not feasible, while a Go outcome means that the study can continue, with or without modifications [44]. The outcomes will be determined after assessing the study data. We will stop if (1) no positive change approaching significance in any of the primary outcomes in SC+: survivors’ housing knowledge, housing self-efficacy, or staff trust, relative to SC, is observed; or (2) survivors, on average, do not intend to continue the use of the tool, as measured by scores of 2=Disagree or 1=Strongly Disagree on the Likert scale. Criteria #1 and #2 will help us determine whether SC+ shows promise of a positive effect and acceptability (as determined by intent to use) to warrant a subsequent intervention trial to a larger group. If either Stop criterion is met, then the full-scale study is not feasible.

If both Stop criteria are not met, then we can move to a Go, that is, continue to a large-scale trial. Modifications will be needed if (1) 75% or more of the questions in the survey are left unanswered, (2) 75% or more of potential survivor participants do not join the study, or (3) less than 95% of enrolled survivors do not complete both the baseline and follow-up surveys. This retention rate is informed by the retention rates of the web-based myPlan evaluation, which hovered around 94% at 6 months and 93% at 12 months [27]. The Go criteria will help us determine whether the study could enroll and engage sizable participation, as illustrated by the rates of recruitment, retention, and response. 

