#### Large-Scale Trial Feasibility

To determine the feasibility of a full-scale trial, we will look at response rates, ease of implementation, and outcome appropriateness, as well as learn how participants respond to the instruments. The response rate on the surveys will serve as a proxy of instrument feasibility and will be calculated as the number of items answered on a survey divided by the total number of survey questions. A “does not apply” answer will count as an item nonresponse, or unanswered. If a 75% response rate or higher is achieved, then the instrument will be deemed feasible. A list of the questions that were answered versus unanswered will also be compiled to improve the instruments.

Ease of implementation, on the other hand, will be measured solely in the key informant interviews. Staff will be asked open-ended questions on their experiences with participant recruitment and use of the tool, for example, “What were some facilitators or challenges to recruiting participants?” “...to the use of the tool in your meetings?”

Perceived outcome appropriateness, finally, will be measured qualitatively through questions on the SC+ follow-up survey and informant interviews on whether housing knowledge, self-efficacy, and staff trust were appropriate to measure for the tool, as well as whether participants recommended other outcomes to measure.

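### The survey-response trigger for modifications is set at 75% unanswered, which is not the complement of the protocol's own standard of 75% answered

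*Protocol article*

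**What the plan says.** The protocol article sets a threshold for survey response in two places.

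- **Large-Scale Trial Feasibility.** The response rate serves as a proxy for instrument feasibility and "will be calculated as the number of items answered on a survey divided by the total number of survey questions". A does-not-apply reply counts against it: such an "answer will count as an item nonresponse, or unanswered". The standard follows: "If a 75% response rate or higher is achieved, then the instrument will be deemed feasible". The section also plans a list of answered and unanswered questions for revising the instruments.
- **Feasibility Criteria.** Once neither Stop criterion is met, the study is a Go, and three conditions call for modifications. The first is that "75% or more of the questions in the survey are left unanswered". The section says that these criteria show whether the study can enrol and engage enough people, "as illustrated by the rates of recruitment, retention, and response".

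The second section does not refer back to the 75% standard in the first, and neither describes a middle category.

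**The concern.** The same figure, 75%, appears once as a share answered and once as a share unanswered. If the trigger was meant to express failure of the instrument standard, the number was not inverted when the sentence was put in the negative. The printed trigger is then far more lenient than the standard it should enforce.

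Feasibility is the primary objective of the study, and instrument feasibility is part of research question 4. The Stop or Go criteria are described as formal and are to be applied after the data have been assessed. With two unreconciled thresholds for one rate, a middling result could be reported as missing the instrument standard or as needing no modification. The choice between the two would be made with the data in view.

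**Working it through.** **Inputs**

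- Response rate r = items answered / total survey questions (Large-Scale Trial Feasibility).
- Instrument standard: feasible if r ≥ 75% (same section).
- Modification trigger (1): unanswered share ≥ 75% (Feasibility Criteria).

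**Same quantity?** The first section computes the rate on a survey. The second speaks of questions in the survey and says that its criteria reflect response. Every item is either answered or unanswered, because a does-not-apply reply is assigned to unanswered. So unanswered share = 100% − r.

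**Trigger (1) on the scale of r.** 100% − r ≥ 75% gives r ≤ 25%.

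**Complement of the instrument standard.** Not (r ≥ 75%) is r < 75%, which gives an unanswered share > 25%. The printed trigger (≥ 75% unanswered) does not follow from the standard.

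**Both rules side by side**

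| Response rate r | Instrument standard (r ≥ 75%) | Trigger (1) (r ≤ 25%) | Consistent? |
|---|---|---|---|
| r ≤ 25% | not met | modification | yes |
| 25% < r < 75% | not met | no modification | no |
| r ≥ 75% | met | no modification | yes |

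The band is open at both ends, since the rules agree at exactly 25% and exactly 75%. Its width is 75 − 25 = 50 percentage points. At r = 40%, for example, 60% of questions are unanswered: the standard is missed and the trigger is silent.

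**On a 10-item scale** (an illustration of granularity; the protocol's rate is taken over the whole survey):

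- 0 to 2 answered: standard missed, trigger fires.
- 3 to 7 answered: standard missed, trigger silent.
- 8 to 10 answered: standard met, trigger silent.

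**After correction** (modification if r < 75%), the inconsistent band is empty: 0 to 7 answered calls for modification and 8 to 10 meets the standard.

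The article does not say whether the rate is pooled over participants or taken per participant. The mismatch is the same either way.

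**The case against.** The best defence is that both rules are one-directional. One says when an instrument is feasible and the other says when modifications are needed; neither says *only if*, and nowhere is a rate below 75% called infeasible in words. Read literally, rates between 25% and 75% are unassigned rather than given opposite verdicts. This is correct as far as it goes, and it limits the wording of the point: the standard is not met and no modification is called for. It does not remove the fault, because a formal criterion that leaves half the scale unassigned, with no stated middle tier, still cannot be applied.

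Three stronger readings are tempting, and the document does not support them.

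- *A survey with most items blank would enter the full trial untouched.* The article plans an item list for revising the instruments whatever the rate, so some revision lies outside the trigger. Unanswered also includes does-not-apply replies, so it does not mean blank.
- *The error could turn a Stop into a Go.* The Stop criteria concern the outcome changes and the intent to continue using the tool. Trigger (1) acts only within a Go, and Hypothesized Findings already expects a Go that is likely to need modifications. The response rate is also only one of several elements used for research question 4.
- *Counting does-not-apply as nonresponse distorts the rate.* The rule is stated openly and is defensible: such a reply gives no value on the 1 to 4 scale, and many of them would signal that items do not fit this population. Nor does it readily push a full responder below 75%. Eight such replies give 22/30 = 73.3% on the 30 outcome items alone. Adding the seven baseline sociodemographic variables, or the five usability and two intent items in the SC+ follow-up, gives (37 − 8)/37 = 29/37 = 78.4%, which passes. The second figure assumes one item per variable. The result depends on the denominator, so it is no finding.

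**Conclusion.** The point holds as a threshold mismatch. Trigger (1) is not the complement of the instrument standard, and for response rates above 25% and below 75% the standard is missed while the formal criteria ask for no modification. The mismatch covers 50 of 100 percentage points.

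This rests on two readings: that both sections refer to the same survey response rate, which the definition and the reference to response support, and that a stated pass mark of 75% is not met below 75%. An un-inverted figure is the likely cause, but that is an inference; the mismatch stands whatever its origin.

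The consequence is limited to research question 4 and to a Go with or without modifications. No effect estimate or Stop decision depends on it. It still needs correcting, because a formal decision threshold is wrong as printed.

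**What to change.** Reword trigger (1) under Feasibility Criteria to: *fewer than 75% of survey questions are answered (more than 25% unanswered)*. This matches Large-Scale Trial Feasibility and closes the band. If two tiers were intended, the article should say so and state what follows between 25% and 75%.

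The cost is one wording edit, with no new data and no change in sample size. The downside is a stricter modification criterion than the one printed, so a Go without modifications becomes harder to reach. SC recruitment ended in April 2023 and those surveys are already in hand. The change should therefore be dated, with a note on whether SC response rates had been seen, and made before the SC+ rates are assessed. The handling of does-not-apply replies can stay as written.

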#### Sample Size, Recruitment and Retention Rates, and Timeline

We will estimate the desired sample size for a full-scale trial based on the effect sizes achieved in this study in the housing knowledge, housing self-efficacy, and staff trust variables. Both the rates of recruitment and retention will be measured quantitatively; the recruitment rate will be defined as the number of participants who enroll divided by the total number of participants recruited, while the retention rate will be defined as the number of participants who complete the follow-up survey divided by the number of participants who complete the baseline survey. Finally, the timeline, or the time it takes to recruit participants, will be recorded to give a benchmark for the full-scale intervention trial.

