## Results

Recruitment for the SC arm began in March 2022 and completed in April 2023. Of the prospective participants, 75 participants were screened, 44 participants were deemed eligible, 35 participants were enrolled (ie, consented to the study), and 23 participants completed both baseline and follow-up surveys. Initially, we had sought to attain 50 completed surveys, 25 in each arm. However, the recruitment timeline for SC took longer than anticipated, and the enrollment numbers were lower than expected. Following 1 year of recruitment for SC that resulted in 23 completed surveys, we sought to expedite the recruitment timeline for SC+. Recruitment for the SC+ arm started in January 2024 and is anticipated to end by May 2024. After SC+ arm recruitment ends, we plan to recruit, conduct, and complete the key informant interviews in June 2024. We subsequently expect to complete the study and be ready to analyze the results by the end of June 2024.

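### The retention trigger is worded in reverse, so it literally asks for modifications at any retention above 5%, and its denominator differs from the protocol's own retention rate

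*Protocol article*

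**What the plan says.** Feasibility Criteria lists three conditions under which a Go needs modifications. The first two are that "75% or more of the questions in the survey are left unanswered" and that "75% or more of potential survivor participants do not join the study". The third is that "less than 95% of enrolled survivors do not complete both the baseline and follow-up surveys". The article then explains the 95% (the last number is a time in months): "This retention rate is informed by the retention rates of the web-based myPlan evaluation, which hovered around 94% at 6 months and 93% at 12".

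The section Sample Size, Recruitment and Retention Rates, and Timeline defines the retention rate as "the number of participants who complete the follow-up survey divided by the number of participants who complete the baseline survey".

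Results gives the SC counts: "35 participants were enrolled (ie, consented to the study), and 23 participants completed both baseline and follow-up surveys". Under Procedures, the consent click comes first. The baseline survey follows and stays open for one week.

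**The concern.** There are two separate problems.

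**Direction.** The first two triggers pair a high percentage with a bad outcome (questions unanswered, people not joining), which is coherent. The third pairs a less-than sign with a bad outcome (not completing). Taken as written, good retention sets it off and near-total loss does not.

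**Denominator.** The trigger counts against everyone enrolled, and enrolled means consented. The defined retention rate counts against those who finished the baseline survey. Someone who consents but never completes the baseline survey lowers the first figure and does not enter the second.

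The third research question asks whether the expected recruitment and retention rates were achieved, and these are formal criteria to be applied once the data are in. If neither the direction nor the base is settled by the text, both must be settled by whoever applies the rule after seeing the results.

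**Working it through.** **Inputs**
- Trigger: non-completion below 95% of enrolled (Feasibility Criteria).
- Benchmark: retention of about 94% at 6 months and 93% at 12 months (Feasibility Criteria).
- SC arm: 35 enrolled, 23 completed both surveys (Results).
- SC baseline completers, *b*: not stated. Assumed range 23 to 35, since at least the 23 who completed both surveys and at most the 35 enrolled can have completed baseline.

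The 95% is a chosen cut-off, not a derived figure, so there is no calculation of the plan's to reproduce.

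**Step 1: direction.** Let R be the share of enrolled survivors who complete both surveys.
- Literal rule: modify if (1 − R) < 0.95, which is R > 0.05.
- Rule implied by the benchmark sentence: modify if R < 0.95.

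With 35 enrolled:

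| Completers | R | Non-completion | Literal rule | Intended rule |
|---|---|---|---|---|
| 0 | 0% | 100% | no modification | modify |
| 1 | 2.9% | 97.1% | no modification | modify |
| 2 | 5.7% | 94.3% | modify | modify |
| 23 (SC as reported) | 65.7% | 34.3% | modify | modify |
| 33 | 94.3% | 5.7% | modify | modify |
| 34 | 97.1% | 2.9% | modify | no modification |
| 35 | 100% | 0% | modify | no modification |

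The rules disagree at 0, 1, 34 and 35 completers and agree at every count from 2 to 33. In general they disagree only when R is at least 95% or at most 5%.

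**Step 2: denominator.** Take the intended direction (modify below 95%).
- Enrolled base: 23/35 = 65.7%, so modify.
- Baseline-completer base: 23/*b*.

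| *b* | 23/*b* | Below 95%? |
|---|---|---|
| 23 | 100% | no |
| 24 | 95.8% | no |
| 25 | 92.0% | yes |
| 30 | 76.7% | yes |
| 35 | 65.7% | yes |

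SC retention therefore lies anywhere from 65.7% to 100% under the outcome-section definition. The verdict changes with the base only if *b* is 23 or 24.

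**Step 3: could the wording matter at the planned size?** The article does not say whether the trigger applies per arm or to both arms together.
- *Pooled (an assumption).* With n enrollees in the tool arm (SC+), all completing, 95% is reached when (23 + n)/(35 + n) ≥ 0.95, so 0.05n ≥ 33.25 − 23 = 10.25 and n ≥ 205. With no SC+ completers, 5% is reached when 23/(35 + n) ≤ 0.05, so 35 + n ≥ 460 and n ≥ 425. The original aim was 25 completed surveys per arm, so neither end is in reach and the readings agree.
- *Per arm.* The readings could part in SC+, but only at 95% or more, or at 5% or less.

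**The case against.** The best defence is that this is a drafting slip whose meaning nobody would miss. The following sentence calls the 95% a retention rate and cites benchmarks just under it, so a reader can recover a completion floor. The trigger is also not a Stop rule: it decides only whether a Go comes with modifications, and Hypothesized Findings already expects modifications to recruitment and retention. On the reported SC counts with the enrolled base, the literal and intended readings give the same answer. All of this stands, and it limits the weight of the point. It does not make the sentence correct, and nothing else in the article restates the rule properly.

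On the denominator, one can say that the 100% figure is extreme. It needs all 12 enrolled non-completers to have missed the baseline survey, although that survey is sent as soon as they consent. That is fair: the two definitions plainly differ, but the size of the difference for SC is unknown.

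Two stronger readings are tempting, and the documents do not support them.
- A reader might infer that the wording will produce a wrong feasibility decision. The counts do not show this: SC is in the range where both readings agree.
- A reader might infer that recruitment has the same conflict, since its rate is "the number of participants who enroll divided by the total number of participants recruited" while its trigger speaks of potential participants. These terms are loose, but they are not defined in ways that contradict each other. On the counts given, non-joining is 1 − 35/75 = 53.3% of those screened or 1 − 35/44 = 20.5% of those eligible, and both are below the 75% trigger.

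**Conclusion.** The third trigger is wrong as written and should be corrected. Literally, it calls for modifications at any retention above 5%, including perfect retention, and for none at 5% or below. The adjacent benchmark sentence shows that a 95% completion floor was meant. Separately, the trigger and the defined retention rate use different denominators. SC is 65.7% on the enrolled base and between 65.7% and 100% on the baseline-completer base.

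The practical effect is limited: SC needs modification under either reading on the enrolled base, and the choice of base changes the SC verdict only if exactly 23 or 24 people completed the baseline survey. These conclusions take the counts in Results as reported and rest on the assumed range of 23 to 35 for the unreported number of baseline completers. This is a should-fix wording and definition error, not a threat to the Stop decision.

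**What to change.** In Feasibility Criteria, reword the third trigger so that modifications are needed if fewer than 95% of those enrolled complete both surveys. In Sample Size, Recruitment and Retention Rates, and Timeline, define the retention rate on that same enrolled denominator.

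The change is to wording only and needs no new data: Results already reports both enrolled and completed counts for SC. The cost is that the retention figure may be less favourable than one based on baseline completers. For SC it would be fixed at 65.7%, the bottom of the 65.7% to 100% range.

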### Statistical Analysis

Multiple linear regression models will be used to test the difference-in-difference in means of housing knowledge, housing self-efficacy, and staff trust. The inclusion of independent variables in the models will be determined by prior tests assessing whether any significant differences exist in outcome variables by demographic and moderating variables. The outcomes of interest will also be input as independent variables to determine the association between housing knowledge, housing self-efficacy, and staff trust.

Sample size, the rates of recruitment, retention, and response, and timeline will be recorded. Ease of implementation and outcome appropriateness will be collected through open-ended questions in individual interviews with the key informants, while acceptability and perceived usability will be collected through a mix of Likert scale and open-ended questions in the surveys and interviews.

To analyze the qualitative data, the written answers from the participant surveys and the transcripts from the key informant interviews will be inductively coded using a constant comparative method. Two coders will separately code the transcripts and then compare and iterate for agreement. Interrater reliability will be calculated as the number of codes in agreement, in proportion to the total number of codes [45]. We will iterate our codes until we achieve a minimum 80% agreement on 95% of our code set [45].

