### Description of the Tool

Knowing the above, the study team collaborated with a coalition of domestic violence housing specialists in New York City to create a web-based tool that both screens and educates survivors on affordable housing programs in New York City. Grounded in the process of empowerment [28], the digital tool strives to address survivors’ barriers to housing knowledge while building survivors’ self-efficacy to achieve their housing goals. Taking only a few minutes, the tool starts by collecting survivors’ household size, income, and living situation, and ends by generating curated matches of housing programs based on the survivors’ information (Figure 1). The tool gives the survivor the agency to determine and learn about their options, without the case manager serving as the sole gatekeeper of information. Because it is one tool, the survivor and case manager also reference the same information, thereby, standardizing the process and freeing up the case manager and survivor to focus on applying for housing programs.

It is important to note that the tool neither guarantees the survivor’s access to housing programs nor addresses every housing need of every survivor. Still, the tool introduces survivors to relevant, available housing programs, all from the convenience of their phones. The tool also serves survivors and nonsurvivors alike. Its content on housing programs is broadly relevant to anyone keen to determine their eligibility for affordable housing programs in New York City.

For this feasibility study, the study team will test the concept of the tool with a convenience sample of survivors served by a community-based domestic violence center (site) in New York City. The site serves a wide range of clients and is particularly attentive to the needs of survivors with disabilities.

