### Research Questions

Through this study protocol, we are seeking to answer the following research questions: (1) What is the initial treatment effect of SC+ (standard care plus), as compared to SC (standard care), on survivors’ housing knowledge, housing self-efficacy, and staff trust? (2) What is the estimated sample size needed for a full-scale intervention trial? What is the estimated timeline needed to reach this sample size? (3) Are the expected rates of recruitment and retention achieved? (4) Are the study’s processes and instruments feasible for a full-scale intervention trial? and (5) Is the tool acceptable and usable by survivors and staff?

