#### Sociodemographics

The study will collect sociodemographic information from participants at baseline. Variables include age, gender, income, length of time with the site, prior or current domestic violence exposure, housing status, and experiences of housing instability in the last 6 months.

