#### Housing Self-Efficacy

According to social cognitive theory, the stronger one’s self-efficacy, the higher the goals one sets and the more favorable the outcomes one expects, and vice versa [33]. In Cattaneo and Chapman’s [28] empowerment process model, likewise, self-efficacy drives the rest of the components: power-oriented goals, knowledge, competence, action, and impact. To measure whether the tool improves survivors’ abilities to achieve their housing goals, we have constructed a 10-item Housing Self-Efficacy Likert scale (Table 3), adapted from three existing scales to incorporate housing: the Generalized Self-Efficacy Scale [34], the Financial Self-Efficacy Scale [35], and the Scale of Economic Self-Efficacy [36]. The questions have been constructed using 4 response categories, from 1=strongly disagree to 4=strongly agree. Participants will be asked to rate their level of agreement on questions such as “I can always manage to solve difficult housing problems if I try hard enough” and “If I experience housing trouble, I can usually think of a solution.” To balance the potential “forced-choice” nature of the four categories, a “does not apply” option has also been added.

**Table 3 table3:** Housing self-efficacy scale.

No.	Item
1	I can always manage to solve difficult housing problems if I try hard enough.
2	If I have a housing problem, I can find ways to get what I need.
3	It is easy for me to stick to and accomplish my housing goals.
4	I am confident that I could deal efficiently with unexpected housing events.
5	Thanks to my resourcefulness, I know how to handle unforeseen housing situations.
6	I can solve most housing problems if I invest the necessary effort.
7	I can remain calm when facing housing difficulties because I can rely on my abilities.
8	When I am confronted with a housing problem, I can usually find several solutions.
9	If I experience housing trouble, I can usually think of a solution.
10	No matter what housing problem comes my way, I am usually able to handle it.

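### The treatment-effect regressions choose covariates by significance tests on the outcomes and are not kept apart from models that use the other outcomes as regressors

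*Protocol article*

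**What the plan says.** The Statistical Analysis section of the protocol article makes three statements in sequence. It names the treatment-effect analysis: "Multiple linear regression models will be used to test the difference-in-difference in means of housing knowledge, housing self-efficacy, and staff trust". It says how covariates enter: "The inclusion of independent variables in the models will be determined by prior tests assessing whether any significant differences exist in outcome variables", the differences being by demographic and moderating variables. It then adds: "The outcomes of interest will also be input as independent variables to determine the association between housing knowledge, housing self-efficacy, and staff trust".

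The section does not say whether baseline, follow-up or change values of the other outcomes are entered, and it names no separate association model. It gives no screening threshold and no fixed covariate list.

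The quantity these regressions serve is research question 1: "What is the initial treatment effect of SC+ (standard care plus), as compared to SC (standard care), on survivors’ housing knowledge", with self-efficacy and staff trust as the other two outcomes. None of the five research questions asks how the outcomes relate to each other.

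**The concern.** The protocol expects the tool to move more than one of these outcomes. The Description of the Tool says it addresses "barriers to housing knowledge while building survivors’ self-efficacy to achieve their housing goals". The Housing Self-Efficacy section cites a model in which "self-efficacy drives the rest of the components: power-oriented goals, knowledge, competence, action, and impact". Under Staff Trust, the housing specialists hoped the tool would back up the advice given by staff. A follow-up or change value of one outcome is therefore measured after treatment and may itself carry part of the SC+ effect. Adjusting one outcome for another removes part of what research question 1 asks for.

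The comparison is also non-randomised and sequential, so covariates are there to control confounding. A significance test on the outcome in a small sample is a poor way to choose them, and it leaves the final model open until the outcomes are seen.

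Two decisions depend on the estimate. Stop criterion 1 (Feasibility Criteria) asks for a positive change approaching significance in at least one primary outcome. The full-scale sample size is to be based on the effect sizes achieved here (Sample Size, Recruitment and Retention Rates, and Timeline).

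**Working it through.** The protocol states no alpha, power, effect size or SD for these models, so there is no planned figure to reproduce.

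**Inputs from the protocol.** Three outcomes; 23 SC completers; an initial target of 25 per arm (Results). Total N is taken as 46 (23 + 23) to 50 (25 + 25).

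**Assumed inputs.** Two-sided 0.05; the same standardised effect d on the change in each outcome; a common within-arm correlation ρ between the outcomes.

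**Step 1: other outcomes as regressors.** Regress one outcome on arm and the other two. Each of those two has within-arm slope ρ/(1+ρ), so

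SC+ coefficient = d − 2d·ρ/(1+ρ) = d(1−ρ)/(1+ρ).

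For d = 0.5, with power from 10,000 simulated trials of 25 per arm:

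| ρ | Share kept | SC+ coefficient | Power, other outcomes in |
|---|---|---|---|
| 0.2 | 0.8/1.2 = 67% | 0.33 | 0.20 |
| 0.3 | 0.7/1.3 = 54% | 0.27 | 0.15 |
| 0.5 | 0.5/1.5 = 33% | 0.17 | 0.11 |

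Without the other outcomes the coefficient is 0.50 and power is about 0.41 to 0.42. With only one other outcome added, the coefficient is d(1−ρ): 0.40, 0.35 and 0.25.

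The result does not depend on which outcome causes which. It needs only that the outcomes are correlated within arm and that the tool moves the others. If the tool does not move the others, the subtracted term is zero.

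**Step 2: effect on the full-scale sample size.** N varies as 1/d². The inflation is 1/(0.667)² = 2.25 at ρ = 0.2, about 3.4 at ρ = 0.3 (1/0.54² = 3.43), and 1/(0.333)² = 9 at ρ = 0.5.

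**Step 3: the covariate screen.** The chance that a covariate truly correlated r with the outcome reaches p < 0.05 is, by Fisher z, Φ(atanh(r)·√(N−3) − 1.96). For r = 0.30, atanh(r) = 0.3095.

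- N = 50: Φ(0.3095 × 6.856 − 1.96) = Φ(0.162) = 0.564, so it is dropped 44% of the time.
- N = 46: Φ(0.3095 × 6.557 − 1.96) = Φ(0.070) = 0.528, so it is dropped 47% of the time.

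**Step 4: bias from the screen.** A dropout rate is not a bias, so this was simulated: 25 per arm, true SC+ effect 0, and one confounder with coefficient 0.2, 0.3 or 0.4 on the change score (10,000 trials each).

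| Arm gap in confounder | Bias, never adjusted | Bias, screened | Bias, always adjusted |
|---|---|---|---|
| 0.5 SD | 0.10, 0.15, 0.20 | 0.05, 0.04, 0.01 | about 0 |
| 0.8 SD | 0.16, 0.24, 0.32 | 0.07, 0.05, 0.02 | about 0 |

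The false-positive rate after screening was 5.1% to 5.8%.

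**The case against.** The strongest reply is that the text does not establish that the treatment effect is adjusted away. The sentence on the other outcomes gives its own purpose, which is to study association. The section speaks of models in the plural, so separate association models are possible. It does not say that follow-up values are entered. With separate models, or with baseline values only, nothing in Step 1 applies, and a condensed article may leave such detail to a fuller plan. This stands as a limit on certainty. It does not remove the point: the sentence says the outcomes are *also* entered, directly after the covariate rule for the difference-in-difference models, and no other section keeps the two analyses apart.

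The size of the attenuation depends on assumed effects and correlations. The cited theory links self-efficacy to knowledge but does not mention staff trust. Both observations are fair, which is why a range is given and why the calculation assumes no causal order.

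On consequences, Stop criterion 1 is met only if all three outcomes fail, and Hypothesized Findings says direction matters more than significance. With equal effects the sign survives adjustment. The criterion is nevertheless worded in terms of approaching significance, so lower power still matters.

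On the screen, the reply largely succeeds as to size. Difference-in-difference already removes stable level differences between the arms. Only factors that affect change and differ between the arms cause bias, and the screen removes most of that.

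**Conclusion.** The point holds in conditional form. If follow-up or change values of the other outcomes enter the treatment-effect models, the SC+ coefficient does not estimate the effect in research question 1. Under equal effects and within-arm correlations of 0.2 to 0.5 it keeps about 67% to 33% of that effect. This could contribute to a false Stop and would inflate the full-scale sample size, about 3.4-fold at a correlation of 0.3.

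A reader might infer that the SC+ effect is certainly biased towards zero. The document does not support that, because it fixes neither the time point nor the model in which the other outcomes are used.

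The significance screen is secondary. A reader might take the 44% to 47% omission rate as a measure of bias. For one imbalanced confounder the bias was only 0.01 to 0.07 SD, with little effect on the false-positive rate. What remains is that the outcome data choose the covariates, with no stated threshold or fixed set.

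**What to change.** For each outcome, specify one treatment-effect model containing arm and a short covariate set fixed now, before SC+ data are analysed. Fit it either on change scores or with that outcome's baseline value as a covariate, and state which.

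Take the covariates from those already collected under Sociodemographics, which include "length of time with the site, prior or current domestic violence exposure, housing status". Length of time with the site and housing status are reasonable examples. Study Design says meetings are more frequent in a new client's first month, so time with the site could affect two-week change.

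Delete the significance pre-screen. Keep the other outcomes out of these models, and report associations between knowledge, self-efficacy and trust in separate analyses labelled exploratory, stating which time point is used.

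The change is to wording only and needs no new data. It costs a few degrees of freedom for covariates that may prove unrelated to the outcome.
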